### Study objectives

A primary objective of the SASA! study was to assess the impact of the intervention on the following outcomes: acceptability of intimate partner violence (among all women; all men); acceptability that a woman can refuse to have sex (among all women; all men); past year experience of physical violence from a partner (among women who have had an intimate partner in the past year); past year experience of sexual violence from a partner (among women who have had an intimate partner in the past year); appropriate community response to women experiencing physical and/or sexual IPV in past year (among women who experienced physical and/or sexual IPV in past year); past year concurrent sexual partners (among non-polygamous partnered men).

More broadly, the study will also document the scale and nature of programme implementation over time, investigate the processes and causal pathways through which gender-based violence and HIV behaviours are promulgated and change over time, conduct a costing of the SASA! intervention, and explore the cost-effectiveness of SASA!.

This protocol describes in detail how the first study objective will be achieved. The broader study objectives will be addressed in subsequent publications.

### The SASA! study setting

The SASA! Study involves eight sites in two administrative Divisions of Kampala (Makindye and Rubaga), that have not been previously exposed to SASA! intervention activities. Taken together, they encompass approximately 66,500 households with 251,500 inhabitants. The communities selected to participate in the study are located in impoverished areas of Kampala, home to concentrations of people who have migrated to the city from various other parts of the country in search of employment. Baseline data from this study showed that the communities are relatively young compared to the national average, with over 40% of respondents aged 25 years or under [47] - a reflection of the migration of this age-group for work and study opportunities. Rubaga Division accommodates the seat of the Buganda Kingdom, and the dominant tribe in the study communities is Buganda, with the primary language being Luganda. However, Kampala is culturally diverse and communities are home to people of many different tribes and mother tongues, all able to coexist. Catholicism is the most prominent religion, but Islam, Protestantism and Born Again Christianity are also widely followed [47]. Makindye Division is home to the biggest police barracks in Uganda and a police training school.

More than three-quarters of the respondents in our baseline survey lived in rented accommodation, most used a public tap as their main source of drinking water (61%), and fewer than 10% of households had a flush toilet. A high proportion of men (two-fifths) and women (three-fifths) had either not completed or not progressed beyond primary education. Despite living on extremely low incomes, people are resourceful and resilient. In many areas, local leadership is strong and responsive to community concerns.

The study communities are affected by a high prevalence of HIV. The 2004–2005 Uganda HIV/AIDS Sero-Behavioural Survey estimated the prevalence of HIV in Kampala to be 12% among women and 5% among men, higher than the national average [41]. An important determinant of HIV vulnerability is sexual concurrency - where someone with a primary partner also has other extra-marital sexual relationships. Uganda’s early success in addressing the HIV epidemic was in part attributed to locally generated HIV prevention messages that promoted ‘zero grazing’ [48]. However, in tandem with reports that HIV incidence may again be on the rise, the 2004–2005 Uganda HIV/AIDS Sero-Behavioural Survey documented a rise in the proportion of sexually active men reporting multiple partners, from 25% in 2000 to 2001 to 29% in 2004 to 2005. The respective 2004 to 2005 figure for Kampala was 35% [41].

In the SASA! study baseline survey, 27% of women reported having experienced physical and/or sexual violence by an intimate partner in the past year [47]. Traditional norms about male authority remain an important aspect of family life in urban Uganda, even though chronic poverty often prevents men from living up to their ideal roles as providers, and women from dedicating themselves exclusively to traditional household chores [49]. Behaviours linked to hegemonic masculinity norms, such as a man’s alcohol consumption and reports of multiple sexual partners, have been found to be associated with IPV in Uganda [50,51]. There is also a strong belief that women should not be treated the same way as men [49]. Violence against women is widely tolerated - analyses of the Ugandan national Demographic and Health Survey found that the majority of women (73%) and men (57%) believe that there are circumstances where wife beating is acceptable [52]. Research in the rural district of Rakai showed that women who perceive that their partners are at higher risk of HIV are more likely to experience IPV [51]. Qualitative research also suggests that women still fear getting tested for HIV, disclosing HIV results, and requesting condom use because of fear of IPV [50,53].

### Evaluation design

The study employs a matched cluster randomised design, with randomisation carried out within matched community pairs. As described previously, the comparison groups comprise four intervention communities (receiving the full intervention) and four control communities (receiving only Division level elements of the intervention) (Figure 3). Quantitative data collection will occur before (baseline) and four years after (follow-up) implementation of the intervention. It is important to note that a four-year follow-up period does not equate to four years of programming - barriers to programme activity including political disturbances and the suspension of activities during political election campaigns, mean that the duration of SASA! programming will have been approximately 2.8 years by the time of the follow-up survey. At each time-point, data will be collected from a cross-sectional sample of community members targeted by the intervention, and from community activists.

The primary analysis will compare intervention and control communities at follow-up. This protocol focuses on the CRT element of the evaluation that will assess the impact of the intervention on the outcomes identified in the first trial objective. However, in addition to this, monitoring and evaluation data will be collected throughout the duration of the study, including through repeated rapid assessment surveys of community members. These data will be used to document, among other things, how the intervention is implemented, its evolution in different communities, CA retention/turnover, the people it reaches, diffusion of activities into control communities, barriers to intervention delivery, and other relevant activities and policy changes that occur over the time period of the study.

A complementary ongoing programme of qualitative data collection will also allow more in-depth understanding of the implementation and processes of the intervention, including community perceptions of it, the forms of behaviour change being promoted, and the ways in which change is occurring at different levels and among different groups.

### Site selection and randomisation

Kampala comprises five administrative Divisions. While some SASA! components occur at Division-level, the majority of intervention activities are implemented in more circumscribed communities or sites. Two neighbouring Divisions were purposively chosen for implementation of the Division-level components of SASA!. Within these, eligible sites were identified on the basis of operational and programmatic considerations. Factors considered when delineating eligible sites included population density, geographical area, socioeconomic characteristics, and accessibility to the CEDOVIP office. Eight eligible sites, each comprising one or two parishes, were identified for the study. All were separated from each other by a geographical buffer (at least one parish wide) to reduce the potential for contamination between intervention and control communities.

Sites were matched into four pairs on the basis of qualitative assessments by CEDOVIP staff as to whether the site was densely populated urban or semi-rural, and assessments of the stability/mobility of the local population.

Within each pair one site was randomly selected to receive the complete intervention from the outset of the study, and the other was designated as a control that would receive the full intervention at the end of the study. The randomisation process was conducted in September 2007. The names of the two communities within a matched pair were written on identical pieces of paper which were then folded and put in a bag. One paper was blindly drawn from the bag. The selected name was assigned as an intervention community. Control communities have been receiving Division-level components of the intervention from the outset of the study.

Interviewers conducting the baseline survey were blinded to the allocation of the intervention. However, at follow-up it will not be possible to keep interviewer teams blinded.

### Recruitment and inclusion criteria

The target population for the community survey was chosen to reflect the population most likely to have had repeated and extensive contact with intervention activities and materials, those living in close proximity to the CAs. The sampling frame therefore comprises households situated in all enumeration areas (EAs) in which CAs (in intervention sites) or passive volunteers (in control sites) live.

A multistage stratified random sampling process is used to sample individuals within sites (Figure 5). The primary sampling unit (PSU) is the CA/EA. The second stage of sampling comprises a simple random sample of households within each of the selected PSUs. Finally, in order to ensure the safety and confidentiality of the respondents, a maximum of one person per household is selected to complete the survey. A household selection form is used to ascertain whether the selected household has any members eligible to complete the community survey. Where more than one eligible household member is identified, one is randomly chosen for interview (with no substitutions made for refusals or failure to subsequently contact this person).

**Figure 5 F5:**
[figure not shown]
Baseline sampling strategy.

A person is eligible for inclusion if he/she is between the ages of 18 and 49 years, has lived in the village for at least a year, usually shares meals with the household, and is the same sex as the CA around whom he/she is sampled.

Separate sampling by sex was chosen both for reasons of safety (to reduce the chance that men in the immediate locality are aware of the nature of the questions in the survey and the potential disclosures that may occur), and to reflect the tendency for CAs to work more with community members of the same sex, although this is in no way circumscribed or absolute. It also makes it logistically easier to ensure that the interviewer is the same sex as the respondent.

At the time of writing, increased funding has been made available for the follow-up survey and this will thus take place in all EAs in which intervention or control CAs were recruited at the start of the study. No substitutions will be made in cases where CAs have since moved away, been substituted or been lost for other reasons. At follow-up, a new mapping exercise of households in all the EAs will be undertaken, and the same subsequent sampling stages followed as those used at baseline.

In addition to the community member’s survey, CAs and passive volunteers (in the control populations) are also surveyed at baseline and follow-up.

### Outcomes

Outcomes will be measured four years after implementation through use of an interviewer administered survey. As described previously, due to external factors forcing intermittent interruptions in programme activity, this four year follow-up period equates to approximately 2.8 years of SASA! programming.

The primary outcomes for this study are presented below, along with the hypothesised direction of intervention effect for each:

Acceptability of intimate partner violence (among all women; all men) (decrease);

Acceptability that a woman can refuse to have sex (among all women; all men) (increase);

Past year experience of physical violence from a partner (among women who have had an intimate partner in the past year) (decrease);

Past year experience of sexual violence from a partner (among women who have had an intimate partner in the past year) (decrease);

Appropriate community response to women experiencing physical and/or sexual IPV in past year (among women who experienced physical and/or sexual IPV in past year) (increase);

Past year concurrent sexual partners (among non-polygamous partnered men) (decrease).

Further discussion on the measurement of outcomes is detailed below.

#### Acceptability of violence

Questions on the acceptability of violence were adapted from those used in the WHO multi-country study on women’s health and domestic violence [54]. The original questions used in the baseline questionnaire demonstrated limited validity and reliability in this setting, and were thus adapted and added to. Focus groups and cognitive interviews were carried out to explore cultural frameworks, cognitive structures and meanings of gender-related concepts in the study communities, and a new set of questions developed and tested. Respondents will be asked a series of questions with the introduction: ‘In your opinion, does a man have good reason to hit his wife if…?’ and then presented with a range of scenarios and circumstances to which they have to provide a yes/no response (she disobeys him; she answers back to him; she disrespects his relatives; he suspects that she is unfaithful; he finds out that she has been unfaithful; she spends time gossiping with neighbours; she neglects taking care of the children; she does not complete her household work to his satisfaction; she refuses to have sexual relations with him; she accuses him of infidelity; she tells his secrets to others in the community; he is angry with her). Respondents who answer yes to at least one of these scenarios will be coded as having attitudes accepting of IPV.

#### Acceptability of a woman refusing sex

Respondents are asked the following question: ‘In your opinion, is it acceptable if a married woman refuses to have sex with her husband if she doesn’t feel like it?’ A positive response is taken to indicate acceptability of a woman refusing sex.

#### Measures of IPV

Questions on the occurrence of IPV are based on questions used in the Uganda Demographic and Health Survey [42] and WHO multi-country study on women’s health and domestic violence [55]. Respondents are asked about their experiences of specific acts without reference to leading terms such as *abuse* or *violence*. Questions are shown in Figure 6. Each of the questions is asked in relation to ‘ever’ and ‘in the last 12 months’. An affirmative answer to any of the physical items for the last 12 months is taken to indicate past year physical violence; a positive answer to any of the sexual items for the last 12 months is taken to indicate past year sexual violence.

**Figure 6 F6:**
[figure not shown]
Items used to create composite outcomes for physical and sexual intimate partner violence.

Female reports of experience are chosen over male reports of perpetration because it is anticipated that men are more likely to give socially desirable responses about their own behaviour and thus under-report perpetration. Indeed baseline data from this study revealed that male reports of perpetration were considerably lower than female reports of experience, particularly for the more severe acts [47].

Questions on violence are asked in accordance with international guidelines for the collection of data on violence against women [56]. These guidelines seek to minimise reporting bias and risk of harm posed to the respondents and interviewers involved in the survey. Interviewers, all from the local community, will undergo at least 3 weeks of preparatory training on ethical and methodological issues surrounding the conduct of a survey relating to IPV and HIV. This includes sessions on how to ensure the privacy, confidentiality and safety of the respondent, how to build rapport, and how to talk about difficult topics in a non-judgmental, sensitive and supportive manner. Interviews are conducted in Luganda or English.

#### Appropriate community response to women disclosing violence

This outcome will be measured among women reporting past year experience of physical and/or sexual IPV. Respondents will be asked: ‘When the experiences you have told me about were happening or afterwards, did anyone in your community try to help you?’ (yes/no). Those answering in the affirmative will then be read a series of questions on how that person/those people tried to help them. If the respondent reports that someone tried to help them, and they did so with at least one appropriate response, this will be coded as an appropriate community response. If the respondent reports that no one tried to help them or no one took any appropriate action or offered appropriate advice, this will be coded as a negative response. Appropriate responses reflect actions encouraged by the intervention and include someone taking the following actions: gathering other people from the community to help; knocking on the door to stop the fighting; separating the woman and her partner during fighting; informing the CA, ssenga, LC, police or other authority; talking to the woman afterwards and asking her if she wants them to help; or telling the woman to talk to someone else such as a family member, friend, community activist, LC, ssenga or other authority figure.

When interpreting results for this outcome, it is necessary to consider the complications in inference that arise when measuring intervention impact on a positive outcome that is contingent on a negative outcome (IPV) occurring. If the intervention is successful in reducing violence, then the mix of cases of violence which remain in intervention communities (and thus for which we can measure community response) may not be comparable to the mix of cases of violence occurring in control sites. They may, for example, comprise those cases that are the most hidden, and therefore least likely to elicit a community response (this in itself being a potential reason why the violence has persisted). We therefore surmise that our estimates of intervention impact for this outcome will be conservative, and we can assume a greater effect than that which we are able to observe.

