### Data analysis

#### Primary analysis

The primary analysis will be a cluster-level analysis of the community survey data using a two-stage approach similar to that used in several recent studies evaluating community-based HIV and violence prevention interventions in Africa [25,33]. We will use an unpaired analysis in order to maximise statistical power given the small number of sites randomised [59], and will follow the basic principles for the analysis of cluster randomised trials as set out by Donner and Klar [60].

The analysis will be done on an intention to treat (ITT) basis, whereby data on all respondents are included whether or not they report any contact with the intervention.

Site-level past year prevalence of the outcome will be generated. The geometric mean of site-level prevalences will be calculated for intervention and control villages respectively, and the ratio of these two figures (geometric mean prevalence ratio) used to give us an estimate of crude intervention effect. An unpaired *t*-test will be used to compare the logarithms of the prevalence figures and assess the statistical significance of the difference in outcomes between intervention and control sites.

The generation of adjusted prevalence ratios for each of the outcome measures involves two stages. First an individual-level binary logistic regression model, in which the dependent variable is the binary outcome of interest, will be fitted to data from control villages. Independent variables will include measures of potential confounders (age, sex and baseline EA-level prevalence of the outcome measure of interest). This model will be used to predict the number of people in each site (intervention and control sites) that would be expected to experience the outcome at follow-up in the absence of the intervention. For each site, the ratio of observed to expected (O/E) numbers with the outcome will then be calculated. A geometric mean of these site-level summary measures will be calculated for intervention and control sites respectively, and a ratio of these means used to generate a point estimate of the adjusted intervention effect. As with the crude estimates, an unpaired t-test will be used to assess the statistical significance of this comparison and construct a 95% CI around the adjusted prevalence ratio.

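### The plan reads the community-response estimate as conservative, but the direction of its selection bias is not established and the true effect cannot be assumed to exceed the observed one

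*Protocol article*

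**What the plan says.** The Outcomes section lists as a primary outcome "Appropriate community response to women experiencing physical and/or sexual IPV in past year (among women who experienced physical and/or sexual IPV in past year) (increase"). Its measurement section confirms the denominator: "This outcome will be measured among women reporting past year experience of physical and/or sexual IPV". The same Outcomes list has physical IPV as a primary outcome expected to fall, "Past year experience of physical violence from a partner (among women who have had an intimate partner in the past year) (decrease"), and treats sexual IPV likewise. The women who enter the response analysis are therefore defined by an event after randomisation that the intervention is meant to change.

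The measurement section recognises the problem. If the intervention reduces violence, it says, the mix of remaining cases in intervention sites "may not be comparable to the mix of cases of violence occurring in control sites". One possibility is offered: "They may, for example, comprise those cases that are the most hidden, and therefore least likely to elicit a community response". The conclusion follows directly: "We therefore surmise that our estimates of intervention impact for this outcome will be conservative, and we can assume a greater effect" than the observed one. No scenario pointing the other way is considered.

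The adjusted analysis does not address case mix: "Independent variables will include measures of potential confounders (age, sex and baseline EA-level prevalence of the outcome measure of interest"). Sex is constant for this outcome, and neither age nor baseline prevalence describes the severity, frequency or visibility of the violence.

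**The concern.** An example introduced as a possibility cannot fix the sign of a bias. If the sign is unknown, a ratio above 1 is not a lower bound for the true effect and may even arise with no effect at all.

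This matters more here than in most trials because the plan relies on direction. The section on coherence and plausibility puts the emphasis on whether change lies in the hypothesised direction and whether the outcomes agree with one another, rather than on significance. The Discussion repeats this and calls the estimates unbiased. If a fall in IPV can by itself raise the conditional response ratio, then less IPV together with more response could be counted as two coherent findings when the second is partly produced by the first.

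**Working it through.** **No figure to reproduce.** Tables 1 and 2 cover physical IPV, sexual IPV and concurrency. The article gives no prevalence, precision or effect size for community response, so the stratum values below are assumptions.

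**General form.** Let r be the chance that a case draws an appropriate response, and w the chance that the case still occurs under the intervention. With no effect on response, the observed ratio is E[wr] / (E[w]·E[r]) = 1 + Cov(w, r) / (E[w]·E[r]). It is below 1 if the more visible cases are prevented, above 1 if the less visible ones are, and 1 if prevention is unrelated to r. The article does not fix the sign of Cov(w, r).

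**Illustration A (assumed).** One third of control cases are visible with 60% response; two thirds are less visible with 20%. True effect on response: none.
- Control: 1/3 × 0.60 + 2/3 × 0.20 = 0.333.
- Half the less visible cases prevented: (1/3 × 0.60 + 1/3 × 0.20) / (2/3) = 0.40. Ratio 0.40 / 0.333 = **1.20**.
- Half the visible cases prevented: (1/6 × 0.60 + 2/3 × 0.20) / (5/6) = 0.28. Ratio 0.28 / 0.333 = **0.84**.

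**Illustration B (assumed).** Half the cases are hidden (20% response) and half visible (60%), so control response is 40%. IPV falls by 25%.
- Only visible cases prevented: (0.50 × 0.20 + 0.25 × 0.60) / 0.75 = 0.333, ratio 0.83.
- Both types fall equally: ratio 1.00.
- Only hidden cases prevented: (0.25 × 0.20 + 0.50 × 0.60) / 0.75 = 0.467, ratio 1.17.
- With responses of 30% and 50% instead, the ratios are 0.92 and 1.08; with 10% and 70%, 0.75 and 1.25.
- If the true ratio is 1.3 in both strata, the observed ratio is 1.08 or 1.52. The second overstates the effect.

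**Frequency.** One appropriate response to the year's experiences is enough for success. With an assumed, independent 20% chance per incident, a woman with one incident scores 20% and a woman with five scores 1 − 0.8^5 = 67%. If women with few incidents drop out of the denominator first, the proportion rises with no change in the community.

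**Disclosure.** The section on site selection and randomisation says interviewers cannot be blinded at follow-up. Take 40% of affected women as helped and disclosure of 80% for all in control. The observed proportion is 0.4·d1 / (0.4·d1 + 0.6·d0), where d1 and d0 are disclosure among helped and unhelped women in the intervention arm.
- d1 = 0.9, d0 = 0.8: 0.429, ratio 1.07. With d0 = 0.7: ratio 1.15.
- d1 = 0.8, d0 = 0.9: 0.372, ratio 0.93. With d1 = 0.7: ratio 0.85.

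**Numbers available.** Baseline past-year IPV was 27%. With 75 women per site (the analysable number assumed in Table 1), 0.27 × 75 = 20 contribute. At follow-up, 2,400 / 8 = 300 people per site; if half are women, 0.27 × 150 = about 40, before any reduction in IPV. So few cases are unlikely to settle the case mix.

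**The case against.** The plan does not overlook the conditioning. It raises the problem itself, argues conditionally on a fall in IPV and hedges its conclusion. Response to violence is undefined where there is no violence, so some restriction to affected women is hard to avoid. Its preferred direction also has support in its own theory: improved community response is described as a pathway to less IPV, and violence reduced that way would tend to be violence that others can see. All of this stands. It makes the plan's scenario plausible, but does not turn a possibility into something that can be assumed.

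Three stronger readings are tempting and are not supported.
- **Upward bias is as likely as downward bias.** Nothing in the article shows this. It shows only that the direction is open.
- **The intervention changes which acts women recognise as violence, and so who enters the denominator.** The passage on recognition of sexual coercion concerns community perceptions. The survey asks about specific acts and avoids labels such as abuse, which limits this route. Differential disclosure remains possible.
- **The outcome should be replaced by IPV without appropriate response among all partnered women.** In Illustration A, with no effect on response, that measure is 1/3 × 0.40 + 2/3 × 0.80 = 0.667 per control case. It becomes 1/3 × 0.40 + 1/3 × 0.80 = 0.40 (ratio 0.60) if half the less visible cases are prevented, and 1/6 × 0.40 + 2/3 × 0.80 = 0.60 (ratio 0.90) if half the visible ones are. Both would look like better response when there was none, and the measure largely restates the IPV outcomes.

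Nor can it be said that no case-mix analysis is planned, since a full analysis plan may exist and is not shown.

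**Conclusion.** The inference is wrong as written. The denominator depends on an outcome the intervention aims to change, and the article gives no basis for fixing the sign of the resulting bias. With no effect on response, case mix alone gave ratios of 0.75 to 0.92 or 1.08 to 1.25 in Illustration B, and 0.84 or 1.20 in Illustration A; disclosure alone gave 0.85 to 1.15. These sizes depend wholly on assumed inputs, and some scenarios are extreme: 1.20 needs a one-third fall in IPV confined to less visible cases. What does not depend on them is that the sign follows from which cases stop and who discloses.

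The fault lies in the interpretation, not in the choice to study affected women. It affects one of six primary outcomes and changes no data or test, but it does change what may be concluded, because the plan leans on direction and coherence.

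**What to change.** 1. Delete the sentence that calls the estimate conservative and assumes a greater effect. State that the direction of the selection bias is unknown.
2. State that the observed ratio will not be read as a lower bound and that, when IPV also falls, it will not count as independent support under the coherence criterion.
3. Keep the conditional outcome as the named primary outcome.
4. As supplementary analyses only, from data already collected: (a) compare the types of reported IPV acts among cases by arm, noting that this describes visibility and frequency only indirectly; (b) report, with the same cluster-level method, IPV without appropriate response among all women partnered in the past year, stating that it mixes IPV reduction with response and cannot by itself support a claim of improved response.

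The cost is a reworded paragraph, one derived variable, a little more analysis and a less favourable interpretation. According to the Trial status section the follow-up survey had only just begun, so the change could be made before results are seen.
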